
### Sample size

Power analyses were conducted using Monte Carlo simulations for linear mixed-effects models in R (version 4.4.0) (packages *lme4* and *simr*). For each simulation, medium-sized interaction effects were specified, and different random intercept and slope variances were considered. Power for fixed interaction effects was evaluated using Wald *t*-tests; power to detect inter-individual variability in change over time was evaluated by comparing the models that include a random slope for time to reduced models including only a random intercept. These comparisons were performed using likelihood ratio tests. For primary analyses examining the time x group interaction effect on TIK’s efficacy, the simulation results indicated that, to achieve 80% power at *α* = 0.05, a total sample size of approximately 132 participants is required. Although the study is powered primarily to detect group × time effects and to account for significant inter-individual variability in change over time, exploratory moderation analyses to examine whether pre-test psychosocial risk is a moderator of TIK’s efficacy are also planned. With 132 participants, the power to detect a three-way group x time x psychosocial risk interaction is substantially lower, as expected (approximately 49%), and approximately 286 participants are required to achieve 80% power. Since we anticipate difficulties in recruiting such a large sample, in this trial, findings concerning the moderator role of psychosocial risk will therefore be interpreted cautiously and considered exploratory, while still providing valuable preliminary evidence regarding which families may benefit most from TIK. These results will help generate hypotheses and inform the design of future, larger implementation trials. Considering an attrition rate of 15% [46, 47], we will have to recruit approximately 152 participants to complete the baseline assessment.

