#### Efficacy evaluation

The statistical analyses will be carried out using SPSS and the R software (version 4.4.0). The level of statistical significance will be set at *p* < .05. Descriptive statistics will be computed for all study variables. Pearson/Spearman correlations will be conducted to explore associations between all the study variables at each assessment wave. Pre-test differences between the intervention and control groups will be analyzed regarding sociodemographic and health characteristics (using qui-square tests) and the primary and secondary outcomes using t-tests (for dichotomous independent variables) and one-way ANOVAs (for categorical and ordinal independent variables) to identify potential covariates.

Linear mixed-effects models accounting for repeated measures within participants will be tested to analyze TIK’s efficacy. Time 0 will be defined as the date of the pre-test assessment, time 1 will be the date of the post-test, and time 2 will be the date of the follow-up assessment. Time, group conditions (intervention (coded as 1) vs. control (coded as -1)), and the 2-way interaction time x group conditions will be included in the models as fixed effects. Moreover, for children-related outcomes (i.e., children’s emotional and behavioral functioning), the child will be treated as the primary unit of analysis and models will also include a random intercept and a random slope for time at the child level in order to account for between-child variability in baseline (at pre-test) levels of the outcome variables and between-child variability in change across time. Since both parents may participate in the study, the child-level random effects also allow one to take into account the non-independence of both parents’ reports for the same child. For parents-related outcomes (i.e., parental emotion socialization and parents’ emotional and behavioral functioning), the parent will be treated as the primary unit of analysis and models will include a random intercept and a random slope for time at the parent-level to account for between-parent variability. To account for the nesting of both parents within the same family, a random intercept at the child level will be included.

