Exploratory moderation analyses will be performed in order to examine whether pre-test psychosocial risk is a moderator of TIK’s efficacy. Psychosocial risk, the 2-way interaction time x psychosocial risk, the 2-way interaction group conditions x psychosocial risk, and the 3-way interaction time x group conditions x psychosocial risk will be added to the previous linear mixed-effects models as fixed effects. Significant interactions with the continuous predictor (i.e., psychosocial risk) will be interpreted and graphed using one standard deviation above and below the grand mean as high and low values.

All linear mixed-effects models will be estimated using maximum likelihood, and the models’ assumptions will be validated by analyzing residual graphs. Deviance difference tests will be performed between a baseline growth model with only time as a fixed effect and models with the predictors to examine model fit improvements. All models will be adjusted for the covariates identified in the preliminary analyses. One model per outcome variable will be performed. Effect size measures will be calculated, namely the ICC (intraclass correlation coefficient) for random effects and Cohen’s *f*^2^ for fixed effects, following the guidelines of Lorah [79]. These analyses, including the calculation of the effect sizes, will be performed using the package *lme4* from R.

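### As described, the efficacy model treats time as linear over 0, 1, 2, so with complete data the post-intervention visit has no weight in the time × group estimate and the end-of-programme effect cannot be estimated

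*Protocol article*

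**What the plan says.** All places are in the protocol article. Under Efficacy evaluation the visits are given numbers: "Time 0 will be defined as the date of the pre-test assessment, time 1 will be the date of the post-test", and follow-up is time 2. Time, group (+1 or −1) and their product are the fixed effects: "the 2-way interaction time x group conditions will be included in the models as fixed effects". For parent outcomes, which include every primary outcome, "models will include a random intercept and a random slope for time at the parent-level to account for between-parent variability", and for families with two participating parents "a random intercept at the child level will be included". The comparison model is "a baseline growth model with only time as a fixed effect".

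Under Sample size, "Power for fixed interaction effects was evaluated using Wald" t-tests, which is a test of a single coefficient.

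No factor coding of time, quadratic or piecewise term, or separate T1 or T2 contrast is stated. The Objectives word the hypothesis as change from before the intervention to follow-up. Study procedures and The intervention place the six weekly sessions between T0 and T1, and the booster after the T2 questionnaires.

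**The concern.** A straight line over 0, 1, 2 says that half of the follow-up benefit is present when the programme ends and that the other half arrives in the two months after the sessions stop. With no session between T1 and T2, a jump at T1 followed by a plateau or a fade is at least as plausible.

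The trial measures every outcome at T1. If the line is the only efficacy model, it cannot say how large the effect was at programme end or whether that effect was maintained. An effect that peaks at T1 and fades would mostly go undetected.

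**Working it through.** **The plan's own figure.** The article gives 132 participants for 80% power with "medium-sized interaction effects were specified, and different random intercept and slope variances were considered", but no numerical effect or variances. The nearest closed form, d = 0.5 in a two-group comparison, gives 2(1.96 + 0.84)²/0.5² ≈ 63 per arm (126 in total), or 64 per arm (128) with the t-test. These are close to 132, but the simulation inputs are not given, so 132 can be neither confirmed nor refuted.

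**Is time linear?** The 0/1/2 coding, the single product term, the random slope, the growth-model label and the one-coefficient test all point to numeric time. If time were a factor, a random intercept plus slopes would need three random effects per parent from at most three observations. These could not be separated from the residual variance.

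**Weights.** The generalised least squares estimate is (X′V⁻¹X)⁻¹X′V⁻¹y, with X holding a constant and time 0, 1, 2, and V = ZDZ′ + σ²I. For every variance set tried, with or without a family intercept, the slope weights on T0, T1, T2 are (−0.5, 0, +0.5). With ±1 group coding, the coefficient is

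[(T2 − T0) in TIK − (T2 − T0) in control] / 4.

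As a check, 66 per arm were simulated with complete data. Adding 1.0 to every TIK score at T1 left the coefficient at 0.1090. Its standard error rose from 0.042 to 0.052 (the fitting gave convergence warnings).

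If time were entered in months (assumed 0/1.4/3.4 or 0/2.4/4.4), the T1 weight would be −0.12 or +0.06 relative to about 1 for T0 and T2.

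**What the line reports.** The intercept weights are (5/6, 1/3, −1/6). Including the group term, the fitted arm differences in SD are:

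| True T0 / T1 / T2 | Intercept | Slope | Fitted T0 / T1 / T2 |
|---|---|---|---|
| 0 / 0.5 / 0.5 | 0.083 | 0.25 | 0.08 / 0.33 / 0.58 |
| 0 / 0.5 / 0.25 | 0.125 | 0.125 | 0.125 / 0.25 / 0.375 |

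The T1 difference is understated, and a baseline difference appears that does not exist.

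**Power.** Alpha is 0.05 ("The level of statistical significance will be set at *p* < .05"), taken as two-sided. Variances are assumed, with total baseline variance 1.

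*By correlation, 65 per arm* (152 × 0.85 = 129.2 in total). SE of the T2 change difference = √[2(1 − ρ) × 2/65]. For a true T2 effect of 0.25 SD:
- ρ = 0.4: SE 0.192, power 25%.
- ρ = 0.6: SE 0.157, power 36%.
- ρ = 0.8: SE 0.111, power 62%.

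A separate T1 contrast of 0.5 SD with a T0–T1 correlation of 0.65 has SE √[2(0.35) × 2/65] = 0.147 and power 93%.

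*By variance components, 66 per arm* (intercept/slope/residual 0.5/0.02/0.5 and 0.6/0.05/0.4). For example, Var(T2 − T0) = 4 × 0.02 + 2 × 0.5 = 1.08, so SE = √(1.08 × 2/66) = 0.181, and 0.25/0.181 = 1.38 gives 28%.

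| True T1 / T2 effect | Slope test | T1 contrast | 2-df factor test |
|---|---|---|---|
| 0.5 / 0.25 | 28–30% | 81–88% | 72–81% |
| 0.5 / 0 | 5% | 81–88% | 85–92% |
| 0.5 / 0.5 | 79–82% | 81–88% | 83–87% |
| 0.25 / 0.5 | 79–82% | 30–34% | 70–73% |

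**Loss after T1.** With all 15% attrition placed after T1, twice the fitted slope is 0.52–0.53 for a true plateau of 0.50.

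**The case against.** The strongest defence is that the slope test answers the hypothesis as written. With complete data it is the T0-to-T2 contrast, rescaled, so the primary test is not wrong. That stands. It is also fair that linear time is inferred and that this is a condensed article. But the article does fix the coding, the fixed effects and the random effects, and those choices determine the estimate.

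A reader might draw four stronger conclusions that the documents and the arithmetic do not support:

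- *That T1 is irrelevant to the test.* It has no weight in the estimate but enters the residual variance and so the standard error. Descriptive statistics for all study variables are also planned, though they are not a test at T1.
- *That a plateau would be missed.* Power is 79–82% for the slope test against 83–87% for the 2-df test. For a truly linear effect the slope test does better than the 2-df test.
- *That recoding time lifts power from 36% to 93%.* Those figures belong to two different contrasts. With T2 as primary, power for a faded effect stays at 36% under the same assumptions.
- *That dropout after T1 doubles the reported effect.* The line does project a T1 plateau to twice its size for one lost parent. At trial level, with 15% loss, the bias is about 0.02–0.03 SD.

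**Conclusion.** The point holds in limited form. As described, the model gives a T0-to-T2 contrast that suits the stated hypothesis, but it cannot estimate the end-of-programme effect or distinguish it from maintenance.

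Where the true T1 difference is 0.5 SD, the model reports about 0.33 (plateau) or 0.25 (fade to 0.25 SD), with a spurious baseline difference of about 0.08 or 0.125. These values follow from the coding and do not depend on the variances when data are complete.

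Power does depend on assumed variances. It is about 28–36% if the effect halves by T2, with a range of 25–62% for T0–T2 correlations of 0.4–0.8. It is 5%, the false-positive rate, if the effect has gone by T2. All of this rests on reading time as numeric, which the description supports but does not state.

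**What to change.** Under Efficacy evaluation, enter time as a three-level factor with group × time terms and an unstructured within-participant covariance in place of the random slope, and keep the family random effect. Report the arm difference with its 95% CI at T1 and at T2. Name T2 as primary, in line with the Objectives, and T1 as a prespecified key contrast. Reword the growth-model comparison to match, and rerun the power simulation for the single T2 contrast.

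With complete data the T2 estimate is unchanged. What is gained is the T1 contrast, not more power at T2. Testing T2 as a single contrast also avoids the loss of a 2-df test when the effect is truly linear (70–73% against 79–82%).

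The cost is a few more covariance parameters, a different R function, and two contrasts per outcome instead of one. Planned recruitment runs to 28 February 2027, so the change can be made before outcome data are complete.

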## Methods

### Trial design

The clinical trial is registered at ClinicalTrials.gov (Identifier: NCT07350083, date assigned January 13, 2026). Ethical approval to conduct this clinical trial was obtained from the Ethics Committee of the School of Psychology and Life Sciences of Lusófona University (Ref. CEDIC-2025-10-30/CEDIC-2025-5-35). The clinical trial will be conducted in compliance with the American Psychological Association [40] guidelines and the Declaration of Helsinki [41]. The study protocol of this clinical trial follows the SPIRIT (Standard Protocol Items: Recommendations for Intervention Trials) guidelines [42] and the reporting of the RCT will followCONSORT guidelines [43].

This study is a parallel two-arm randomized controlled trial that will be conducted between December 2025 and December 2027. After completing the baseline assessment, participants will be randomly allocated to either the intervention group or the control group (allocation ratio 1:1). A wait-list group will be used to minimize threats to internal validity and because it has been considered ethically acceptable for preventive interventions [44]. Participants in the control group will receive the intervention after the follow-up assessment.

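### The efficacy models estimate a baseline difference between arms that randomisation has set to zero; giving both arms one pre-test mean would recover the lost precision, by an amount the protocol does not let us fix

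*Protocol article*

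**What the plan says.** All references are to the protocol article.

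- **Efficacy evaluation.** The baseline is a response in the model: "Time 0 will be defined as the date of the pre-test assessment", followed by the post-test and the follow-up. Group is coded +1 and -1. Time and group enter as fixed effects, and "the 2-way interaction time x group conditions will be included in the models as fixed effects". For parent outcomes, which include all the primary outcomes, "models will include a random intercept and a random slope for time at the parent-level".
- **Trial design** (Study procedures agrees): "After completing the baseline assessment, participants will be randomly allocated".
- **Sample size.** The power target is the interaction: "For primary analyses examining the time x group interaction effect on TIK’s efficacy", a total of 132 is said to give 80% power. The inputs are described only in words: "medium-sized interaction effects were specified, and different random intercept and slope variances were considered".
- **Efficacy evaluation, on covariates.** The arms are compared at pre-test on background characteristics and on the primary and secondary outcomes. All models are then adjusted for whatever those comparisons identify. No rule adjusts for the baseline outcome in every case.
- **Efficacy evaluation, on model fit.** The deviance test compares a model containing only time with the models containing the predictors.
- **Nonadherence, attrition and missing data.** Everyone who completed the baseline assessment is to be analysed.

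**The concern.** With time zero at the pre-test, the group coefficient represents the baseline difference between arms (half of it under +1/-1 coding). Because allocation comes after that measurement, its true value is zero by design, and any observed difference is chance. Estimating it freely discards that knowledge, so the time by group term compares change from baseline between arms.

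Two things follow. The treatment contrast has a larger variance than one that uses the baseline as a common starting point. And, conditional on a chance baseline gap, regression to the mean carries part of that gap into the estimate with the opposite sign. The first affects every primary and secondary outcome in a trial whose stated target is 80% power.

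**Working it through.** **The plan's own figure.** The total of 132 cannot be reproduced, because the effect is given only as medium and no SD, correlation or variance component is stated. The nearest simple variant is a difference of 0.5 SD of change, two-sided 5%, 80% power. It gives 126 in total by the normal approximation or 128 by the t distribution, and 66 per arm gives 81–82% power. The missing correlation therefore cannot be recovered from the sample size, and every size below rests on assumed values.

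**What the planned contrast is.** With complete data and waves coded 0, 1, 2, the fitted slope contrast is (T2 − T0)/2. With time as a factor it is T2 − T0 or T1 − T0. Either way it is raw change. With missing visits this is only approximate.

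**One post-baseline wave, equal SDs of 1, correlation rho (assumed).**

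- Variance of change: 2(1 − rho).
- Variance with a common baseline mean: 1 − rho².
- Ratio: (1 + rho)/2, so the reduction is (1 − rho)/2.

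| rho | change | common baseline | reduction |
|---|---|---|---|
| 0.4 | 1.20 | 0.84 | 30% |
| 0.5 | 1.00 | 0.75 | 25% |
| 0.6 | 0.80 | 0.64 | 20% |
| 0.7 | 0.60 | 0.51 | 15% |
| 0.8 | 0.40 | 0.36 | 10% |

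A simulation of three waves with 15% dropout (66 per arm, 4,000 runs) gave reductions of about 24%, 17% and 13% at rho 0.5, 0.6 and 0.7. Both estimators were unbiased.

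**Linear time with a random intercept and slope, as planned.** Let X have rows (1,0), (1,1), (1,2), and let C = sigma²(X′X)⁻¹ + G be the covariance of one person's fitted intercept and slope. Fixing the intercept difference at zero lowers the variance of the slope contrast by the fraction C12²/(C11·C22). This is a squared correlation and so cannot be negative. Here (X′X)⁻¹ has diagonal 5/6 and 1/2 and off-diagonal −1/2.

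Assumed grid, with total baseline variance 1: intercept share 0.5–0.7, slope variance 0.02–0.10, intercept–slope correlation −0.5 to +0.3. The family-level random intercept is left out.

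- **Smallest gain** (0.7, 0.10, +0.3; sigma² = 0.3). C11 = 0.25 + 0.70 = 0.95. C12 = −0.15 + 0.3·√0.07 = −0.071. C22 = 0.15 + 0.10 = 0.25. Reduction = 0.0050/0.2375 = 2%.
- **Largest gain** (0.5, 0.10, −0.5; sigma² = 0.5). C11 = 0.417 + 0.500 = 0.917. C12 = −0.25 − 0.5·√0.05 = −0.362. C22 = 0.25 + 0.10 = 0.35. Reduction = 0.131/0.321 = 41%.

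The correlation between baseline and follow-up does not settle the gain by itself. Grid points with an implied T0–T2 correlation of 0.66 and 0.53 give about 2% and 32%.

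**Chance imbalance.** With equal SDs, a baseline gap g shifts the change-score estimate by −(1 − rho)g. For g = 0.2 SD, that is 0.10 SD at rho 0.5 and 0.06 SD at rho 0.7, against the direction of the gap.

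**The case against.** The planned specification is a standard mixed model. It is unbiased under randomisation, keeps everyone with a baseline, and tests the same interaction that was powered. All of that stands. A reader might infer that the trial would give a wrong or biased answer, and the documents do not support this: the shift from a baseline gap is conditional on the gap and averages to zero over randomisations.

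A reader might also infer a firm gain of 15–25%, or that 80% power would become 86–90%. Those figures need a correlation of 0.5–0.7, which the protocol does not give, and a two-wave formula with equal SDs. The plan has three waves and a random slope, and its sample size came from simulations over several variance settings.

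Finally, the plan does not ignore baseline imbalance, since pre-test differences on the outcomes can trigger covariate adjustment. That is only a partial answer. It acts only when a difference is observed, so the model depends on the data, and it leaves the precision loss untouched otherwise. Nor can the baseline score properly serve as a covariate while T0 remains a response in the same model.

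**Conclusion.** The point holds as a loss of precision in a valid analysis. The model spends a parameter on a difference known to be zero, and the tested interaction is in effect a change-score comparison. Sharing one baseline mean cannot raise the large-sample variance when the mean model is right. The gain is 10–30% under the two-wave formula at assumed correlations of 0.8 down to 0.4, and about 2% to 41% over the assumed random-slope grid. No single figure can be claimed for this trial. The change is worth making because it uses only data already being collected and applies to every outcome.

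**What to change.** 1. **Main models.** Omit the group main effect and keep time by group, so that both arms share one pre-test mean. With time as a factor, build the T1-by-group and T2-by-group indicators explicitly; simply deleting group from a formula can bring back a T0-by-group column. The factor form is the safer one. Randomisation equates the T0 means, whereas with linear time a shared intercept also assumes that the group difference grows in proportion to time.
2. **Do not treat the baseline-as-covariate model as fully equivalent.** Modelling T1 and T2 with the T0 score as covariate drops participants who have only T0, contrary to the rule that all baseline completers are analysed. The shared-mean model keeps them.
3. **Deviance test.** Compare models that differ only in the time by group term or terms. The present comparison tests the baseline difference and the treatment effect together.
4. **Moderation model.** Omit the group by psychosocial risk term at baseline in the same way, as it too is zero under randomisation. Keep risk, time by risk and the three-way term.
5. **Timing.** Make the change before outcome comparisons are seen. The trial is open-label, and preliminary or partial results are to be shared while it runs.

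The cost is a short amendment and a few lines of code, with no new data, participants or visits. The power simulation would need rerunning only if the stated power is to describe the revised model.

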### The intervention

#### Tuning in to Kids^®^ Intervention

Tuning in to Kids^®^ is an evidence-based parenting program for children aged 3 to 12, designed to foster emotionally responsive parenting, thereby promoting children’s emotional development. Drawing upon research in the field of emotion socialization (e.g., [49, 50], the program is based on the premise that children’s MH difficulties can be reduced through the experience of emotional validation by parents. The TIK program is delivered as a structured, group-based intervention consisting of six 2-hour weekly in-person sessions [9]. A follow-up booster session is included in the program to allow parents to consolidate their learning and address current main challenges. The sessions are conducted by two facilitators in closed groups of 8 to 12 parents. After session 2, no additional participants were allowed to join the group, to facilitate peer support and open discussion. Program content combines psychoeducation, group brainstorming, role-play exercises, video materials, and home practice activities for parents to apply emotion coaching in real-life scenarios. The structured format (see Table 2) provides a supportive environment for parents to reflect on their own meta-emotion and progressively develop the skills to respond to their child ren’s emotions through emotion coaching [51]. More information about the program can be found at the website: https://tuningintokids.org.au/. The Portuguese version of TIK was adapted primarily to ensure linguistic and cultural relevance (i.e., after being translated into Portuguese, the materials were reviewed for cultural appropriateness). Only minor modifications were made, including the adaptation of some examples and references in the program content to better reflect Portuguese family contexts.

**Table 2 Tab2:** Session-by-session description of the Tuning in to Kids^®^ intervention

Session	Themes
1	Introducing the program and the concept of emotion coaching, while creating a warm, non-judgmental environment that normalizes parental challenges and worries, builds emotional awareness, and welcomes participants.
2	Exploring emotion coaching and the concept of meta-emotion by helping participants to reflect on how past experiences with the family of origin and cultural values influence parenting practices and the use of empathetic responses.

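### TIK is delivered in closed groups, but the outcome models have no term for the TIK group and the power description mentions none; if change is correlated within groups, type I error exceeds 5% and a valid test has less than 80% power at 132.

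*Protocol article*

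**What the plan says.** - **Delivery** (Tuning in to Kids Intervention): "The sessions are conducted by two facilitators in closed groups of 8 to 12 parents". Nobody joins after session 2, and groups contain only trial parents. Under Training, supervision, and implementation fidelity, the fidelity checklist is partly meant to allow groups to be compared with one another.
- **Allocation** (Trial design): "participants will be randomly allocated to either the intervention group or the control group (allocation ratio 1:1"). Controls are offered TIK only after the follow-up assessment, so they have no delivery groups while outcomes are collected.
- **Model** (Efficacy evaluation): for parent outcomes, "models will include a random intercept and a random slope for time at the parent-level to account for between-parent variability", with a further child-level intercept for two parents of one child. Child outcomes get a child-level intercept and slope. All models are fitted by maximum likelihood, and deviance tests compare a time-only growth model with models that add predictors. No TIK-group, facilitator or site term is listed.
- **Power** (Sample size): "medium-sized interaction effects were specified" and "different random intercept and slope variances were considered". The conclusion is that "to achieve 80% power at" alpha = 0.05, "a total sample size of approximately 132 participants is required". Neither the effect nor the variances are given as numbers, and no group-level variance is mentioned.

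**The concern.** Parents in one TIK group share two facilitators, a setting and six sessions of discussion and role-play. Their changes may therefore be more alike than those of parents from different groups. Because this can arise in one arm only, the design is partially nested.

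The planned random effects do not absorb the dependence. A parent-level or child-level slope treats each person's change as independent of everyone else's, whereas a shift common to a TIK group moves 8 to 12 parents together. That shift falls directly on the time x group contrast, which is the efficacy test for every primary and secondary outcome.

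The plan does model dependence between two parents of one child, who join together only on request. It leaves out a dependence that could affect everyone attending TIK. The resulting error favours declaring TIK effective. The same gap weakens the power statement if the simulation matched the planned model.

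**Working it through.** **Inputs from the protocol article.** 132 analysed (66 per arm), 80% power, alpha 0.05 (taken as two-sided), 152 recruited (76 per arm), 8 to 12 parents per TIK group. Number of groups: 76/12 = 6.3 to 76/8 = 9.5.

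**Assumed.** ICC of change within a TIK group: 0.01, 0.02, 0.05, 0.10. The ICC of change is the relevant one because groups form after baseline.

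**The plan's own figure.** 132 cannot be reproduced exactly, because the effect and variances are not stated. As a proxy, a standardised difference of 0.5 with independent participants needs 126 in total (normal) or 128 (t), and gives 81.9% or 81.4% power at 66 per arm. So 132 lies close to an unclustered calculation. Below, the effect is set to give exactly 80% at 66 per arm: (1.96 + 0.84) x sqrt(2/66) = 0.488.

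**Group size among those analysed.** Ten is an enrolled size. Scaled to analysed numbers it is 10 x 66/76 = 8.7. Results are shown for m = 8.7 and m = 10.

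**Formulas.**
- Design effect in the TIK arm: DE = 1 + (m - 1) x ICC
- Variance factor for the arm contrast, with clustering in one arm: f = (DE + 1)/2
- Type I error of the planned test: 2 x [1 - Phi(1.96/sqrt(f))]
- Power of a test with the correct standard error, normal reference: Phi(2.80/sqrt(f) - 1.96)
- The same with a t reference: noncentral t with Satterthwaite degrees of freedom, taking 66/m - 1 for the TIK arm and 65 for control

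**Worked case, m = 10, ICC 0.05.** DE = 1 + 9 x 0.05 = 1.45; f = 2.45/2 = 1.225; sqrt(f) = 1.107. Type I error = 2 x [1 - Phi(1.771)] = 7.7%. Power, normal reference = Phi(2.531 - 1.96) = 71.6%. Satterthwaite df is about 15, giving 65.9%.

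| ICC | m | f | Type I error, planned test | Power, groups modelled (normal) | Power, groups modelled (Satterthwaite) |
|---|---|---|---|---|---|
| 0.01 | 8.7 | 1.038 | 5.4% | 78.5% | 74.9% |
| 0.01 | 10 | 1.045 | 5.5% | 78.2% | 73.9% |
| 0.02 | 8.7 | 1.077 | 5.9% | 77.0% | 73.1% |
| 0.02 | 10 | 1.090 | 6.0% | 76.5% | 71.8% |
| 0.05 | 8.7 | 1.192 | 7.3% | 72.8% | 68.2% |
| 0.05 | 10 | 1.225 | 7.7% | 71.6% | 65.9% |
| 0.10 | 8.7 | 1.384 | 9.6% | 66.3% | 60.8% |
| 0.10 | 10 | 1.450 | 10.4% | 64.3% | 57.5% |

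**Check by simulation.** For m = 10, 20,000 simulated trials per ICC, each analysed by a t-test on per-person change that ignores groups, gave type I errors of 5.7%, 7.6% and 10.0% at ICC 0.02, 0.05 and 0.10.

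**The planned test under the assumed effect.** It keeps the too-small standard error, so it rejects with probability Phi(0.84/sqrt(f)): 79.0%, 77.6% and 75.8% at m = 10.

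**The case against.** **The size is conditional.** Standard errors are too small only if change is positively correlated within TIK groups, and the article gives no ICC for any outcome. At ICC 0.01 the type I error is about 5.5% and power with a normal reference about 78%. This stands. A reader might infer that every efficacy test certainly rejects too often; the document supports only the conditional statement.

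**Power of which test?** A reader might take 64% as the power of the analysis as written. It is not: the planned test still rejects about 76% of the time at ICC 0.10, but at an inflated type I error. The lower figures belong to a test that accounts for groups. Since such a test also needs small-sample degrees of freedom, the Satterthwaite column is the more realistic one.

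**The simulation is not shown.** A reader might conclude that it definitely left out the TIK group. The Sample size section only describes random intercept and slope variances and inter-individual variability. Absence of a group component is the likely reading, not an established fact.

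**Could the analysis plan supply the term?** This carries little weight. The article lists the random effects level by level, so adding a group effect would change the published model rather than fill in a detail.

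**The remedy is not free of difficulty.** Deviance tests between models with different fixed effects are not valid under REML, so a wholesale switch would conflict with the stated plan. A group variance estimated from about 6 to 10 groups may also come out at zero or give a singular fit. Both points stand and are dealt with in the fix.

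**Conclusion.** The point holds in conditional form. The delivery format creates about 6 to 10 groups in one arm, and the stated random effects leave them out. For any positive within-group correlation of change, the time x group standard error is too small and a valid test at 132 falls short of 80% power.

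The size rests on assumed ICCs, 66 analysed per arm, about 9 to 10 analysed per group, and an effect calibrated to 80% power without clustering. Over ICC 0.02 to 0.10, type I error runs from about 6% to about 10%, and Satterthwaite-based power from about 73% down to about 58%. At ICC 0.01 the type I error is barely affected.

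The document does not establish that the correlation is present, or how large it is. It is still worth settling before outcomes are analysed: the error favours TIK, it reaches every efficacy test, and a term chosen after seeing the data would be open to question.

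**What to change.** 1. **Record the TIK group ID** for every parent in the TIK arm. Under intention to treat, a parent who never attends keeps the group into which they were booked.
2. **Add to each efficacy model a random effect for TIK group**, active in the TIK arm only, on the change over time.
3. **Test time x group from a REML fit** with Satterthwaite or Kenward-Roger degrees of freedom. Keep maximum likelihood for the planned deviance tests.
4. **Prespecify a fallback for a singular fit**, for example simplifying the other random effects first, or using cluster-robust standard errors with a small-sample correction.
5. **Restate power at the planned size as a range** over an explicit ICC range, and say whether the simulation included a group component.

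**Cost.** One extra variable, revised analysis wording and a rerun of the simulation. Confidence intervals widen and the stated power becomes less favourable. The change makes the test valid but does not restore 80%: with a normal reference and m = 10, that would take 132 x f, or about 144, 162 or 192 analysed at ICC 0.02, 0.05 or 0.10. Recruitment need not change, provided the lower power is stated openly.
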